#### Data monitoring

As a pilot study with a small number of planned participants utilising an established safe allergy assessment protocol, a data monitoring committee will not be established. Any serious adverse events or antibiotic-associated immune-mediated adverse events will be referred to two independent clinicians with extensive experience in antibiotic allergy for adjudication.

Participant retention will be promoted through the offer of telephone follow-up for patients post-hospital discharge.

#### Harms

Serious adverse events (SAEs) will be defined as any adverse drug event that, in the opinion of the investigators, is causal for any of these outcomes: (1) death; (2) life-threatening reaction; (3) inpatient hospitalisation; (4) results in persistent or significant disability/incapacity; (5) congenital anomaly or birth defect; or (6) requires intervention to prevent permanent impairment or damage. SAEs that occur from the time of commencement of study treatment to 5 days after the second challenge/observation will be collected and reported to the approving ethics committee within 24 h of study staff becoming aware of the event.

An antibiotic-associated immune-mediated adverse event will include any immune-mediated reaction within 48 h of an antibiotic dose judged by two independent reviewers. An antibiotic-associated adverse event will be defined as any non-immune mediated reaction (e.g. diarrhoea, nausea and vomiting) within 48 h of an antibiotic dose judged by two independent reviewers.

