**Primary outcome measures**	
* Feasibility outcome measures*	
* Eligibility to screened ratio*	Proportion of patients that are eligible for intervention
*** Recruitment to eligibility ratio***	Proportion of eligible patients consenting to the participation in the study *(a ratio of* ≥ *50% will be used as the primary determinant of feasibility)*
* Intervention to recruitment ratio*	Proportion of patients randomised to the intervention arm that had the intervention delivered as per protocol
* Protocol compliance*	Proportion of randomised patients that complete all study activities as per protocol
* Safety outcome measures*	
* Safety*	Proportion of patients with a penicillin allergy who experience an antibiotic-associated immune-mediated adverse event OR serious adverse event *(a proportion of* < *5% will be used as the determinant of safety)*

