### Blinding

The participant, ICU team and treating clinicians will be blinded to the formal Allergy Assessment Tool result and PEN-FAST score. The participant, ICU team and treating clinicians will not, however, be blinded to the result of eligibility to be randomised (i.e. low risk vs. high risk). The participant, ICU team and treating clinicians will not be blinded to the allocation or outcome of the oral penicillin challenge in participants of the intervention arm.

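### The serious-adverse-event component of the primary safety outcome depends on unblinded investigators' opinion of causality before any independent review

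*Protocol article*

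**What the plan says.** Table 1 of the protocol article defines the primary safety outcome as: "Proportion of patients with a penicillin allergy who experience an antibiotic-associated immune-mediated adverse event OR serious adverse event". The rule attached to it is that a proportion below 5% is the determinant of safety.

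The Harms section defines the two components differently:

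- **SAE component:** "Serious adverse events (SAEs) will be defined as any adverse drug event that, in the opinion of the investigators, is causal for any of these". A list of serious consequences follows, death and life-threatening reactions among them. The causality judgement is the investigators' and is part of the definition.
- **Immune-mediated component:** "any immune-mediated reaction within 48 h of an antibiotic dose judged by two independent reviewers". The same section gives non-immune reactions, such as nausea or diarrhoea, to two independent reviewers as well.

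The Data monitoring section explains that there will be no data monitoring committee and sets the referral rule: "Any serious adverse events or antibiotic-associated immune-mediated adverse events will be referred to two independent clinicians with extensive experience in antibiotic allergy for adjudication".

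The Design and schedule section calls the trial open label. The Randomisation section has study investigators perform the allocation.

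**The concern.** An independent adjudication step should correct attribution errors in both directions. Here the SAE component is filtered before that step. If investigators wrongly attribute a serious event to a drug, the event is an SAE, it is referred, and the adjudicators see it. If they wrongly attribute it to sepsis or another illness, it is not an SAE by definition, and no stated rule sends it to anyone independent. Of the two possible errors, only the one that lowers the event count is sure to go unreviewed.

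This matters because the filter acts on a primary outcome with a fixed pass mark, the people applying it know the allocation, and the two adjudicators are the only independent check on harms that the article describes.

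A second problem is internal. Data monitoring and Harms do not agree on which reactions the independent reviewers see.

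**Working it through.** **Step 1. Trace one event through the text.** Take a patient with a life-threatening deterioration the day after challenge, which the investigator attributes to underlying illness.

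| Section | Rule | Result for this event |
|---|---|---|
| Harms | An SAE must be a drug event that investigators consider causal | Not an SAE |
| Data monitoring | SAEs and immune-mediated events are referred | Not referred |
| Intervention; Control | Reviews look for serious or antibiotic-associated events under the protocol's definitions | Same filter applies |
| Data collection | Records antibiotic-associated adverse events, SAEs included | Attribution is presupposed |
| Table 1 | Counts SAEs and immune-mediated events | Not counted |

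No section provides another route to the adjudicators.

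**Step 2. Compare the two sections on reactions.** Data monitoring names only the immune-mediated category (plus SAEs) for referral. Harms has two independent reviewers judge both immune and non-immune reactions within 48 h of an antibiotic dose. If Harms governs, a rash first taken as non-immune is reviewed and can be reclassified. If Data monitoring governs, it is not referred. Both cannot describe the same process.

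**Step 3. Reproduce the planned size.** The Sample size section gives 200 eligible, 50% recruited and 85% completing: 200 × 0.50 × 0.85 = 85, which matches the stated pool. It then plans 80 enrolments, 40 per arm. Table 1 does not say whether the 5% rule applies to one arm or to all participants, so both denominators are shown.

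**Step 4. Apply the below-5% rule** (events ÷ n, with exact Clopper-Pearson 95% intervals).

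| n | Events | Proportion | 95% CI | Below 5%? |
|---|---|---|---|---|
| 40 | 1 | 2.5% | 0.06% to 13.2% | yes |
| 40 | 2 | 5.0% | 0.6% to 16.9% | no |
| 80 | 3 | 3.75% | 0.8% to 10.6% | yes |
| 80 | 4 | 5.0% | 1.4% to 12.3% | no |

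Moving from fail to pass takes one event, with either denominator.

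**Step 5. Illustrate incomplete capture.** Assume a true event rate p and that each true event is counted independently with probability s. Neither figure is in the documents. The observed count is then binomial with probability p × s, and the rule passes with at most 1 event (n = 40) or at most 3 (n = 80).

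| True rate p | n | s = 100% | 90% | 75% | 50% |
|---|---|---|---|---|---|
| 5% | 40 | 39.9% | 45.7% | 55.5% | 73.6% |
| 5% | 80 | 42.8% | 51.2% | 64.7% | 85.9% |
| 10% | 40 | 8.0% | 11.4% | 18.8% | 39.9% |
| 10% | 80 | 3.5% | 6.3% | 14.1% | 42.8% |

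Cells are the chance of passing. The table shows how sensitive the rule is. It does not estimate how many events this trial would lose.

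**The case against.** **The stronger reading fails.** A reader might infer that adjudication as a whole can only take primary events away and never add one. The documents do not support that. Harms gives both immune and non-immune reactions to two independent reviewers and does not say that investigators decide the mechanism first. A reaction thought to be non-immune could be reclassified and add an event. The one-way gate applies to the SAE component only. Even there, the power to remove an event is an inference, because the article does not say what the adjudicators may change.

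**The Blinding section is weak support.** It says "The participant, ICU team and treating clinicians will not be blinded to the allocation or outcome of the oral penicillin challenge" in the intervention arm, but it does not name the investigators. Their knowledge of allocation follows from the open-label design and from their performing the allocation.

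**The direction of net bias is not shown.** Investigators who know a challenge was given might over-attribute events to it. The most unstable patients are excluded, so one cannot assume that nearly every serious event has a rival explanation. What stands is narrower: over-attribution reaches the adjudicators and under-attribution does not.

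**Deaths are not invisible.** In-hospital and 30-day mortality are exploratory outcomes, compared between groups without a causality filter. That is a partial safeguard. It covers deaths only, involves no causality review, and does not feed the 5% rule.

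**Sensitivity to one event is generic.** Any 5% cut-off at this size behaves this way for any misclassification. This is correct. The arithmetic shows what one lost event can do, not how often one is lost.

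**An article condenses the full protocol.** Adjudication procedures may well be set out there. But the article states both the SAE definition and the referral list, and the concern is with what those two statements do together.

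**Conclusion.** The point holds for the SAE component. Unblinded investigators' opinion on causality decides which serious events can be adjudicated, and a serious event wrongly attributed to illness cannot be recovered by any route described. For the immune-mediated component, the defect is a contradiction between Data monitoring and Harms that must be reconciled.

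The possible consequence is a reversed safety verdict: one unreferred event separates 2/40 (5.0%, fails) from 1/40 (2.5%, passes), or 4/80 (5.0%, fails) from 3/80 (3.75%, passes). The likelihood cannot be derived from the documents.

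Two assumptions are made: that the independent reviewers in Harms are the independent clinicians in Data monitoring, which the text does not say, and that adjudicators may overrule an investigator's attribution. If they may not, investigator opinion settles the SAE component in both directions. The change should be made.

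**What to change.** 1. **Keep the SAE definition for expedited ethics reporting.** Redefining SAEs by outcome alone would send every unrelated serious ICU event to the ethics committee within 24 h. With Table 1 unchanged, it would also put all-cause events into the 5% outcome.
2. **Separate referral from attribution** in Data monitoring and Harms. Refer to the two adjudicators already named, in both arms and within the existing safety window (start of study treatment to 5 days after the second challenge or observation), every event that meets a listed seriousness outcome, whatever the investigator's attribution. Refer every suspected antibiotic reaction too, immune or not, so that the two sections agree.
3. **Amend Table 1** so that the primary safety outcome counts events that the adjudicators judge to be antibiotic-related and serious, or immune-mediated.
4. **Record the investigator's opinion** without letting it determine referral.

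The cost is wording in three places and more case summaries for the adjudicators, many of them on unrelated ICU events, in an 80-patient trial. The adjudicators are those already planned, and ethics reporting is unchanged.

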**Inclusion criteria**
1. Adult (≥ 18 years) ICU inpatient
2. Reported penicillin allergy with a PEN-FAST score < 3
3. Are expected to stay in the ICU at least 24 h post-assessment
**Exclusion criteria** (patient excluded if **ONE** of the following criteria present)
1. Known pregnancy
2. Death is deemed imminent or inevitable during this admission, and either the attending physician, patient or medical treatment decision-maker is not committed to active treatment
3. Any other illness that, in the investigator’s judgement, will substantially increase the risk associated with subject’s participation in this study
4. Patients with known history of ANY non-penicillin drug-associated anaphylaxis
5. Patients with a known history of idiopathic urticaria, idiopathic anaphylaxis or mastocytosis
6. Patients where the allergy history was not able to be confirmed with patient or medical treatment decision-maker
7. Patients on antihistamine therapy (excluding H2-receptor antagonists)
8. Patients receiving > 10 µg/minute of noradrenaline or any adrenaline therapy in the last 4 h
9. High ventilator requirement if intubated (any of the following) i. Any mode other than spontaneous ii. Peak end-expiratory pressure (PEEP) > 5 cm H2O iii. FiO2 > 40%
10. Patients receiving more than stress dose steroid therapy (i.e. > 50 mg QID hydrocortisone or daily equivalent)

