### Intervention and control arms

#### Intervention

The intervention is a single dose 250 mg of oral penicillin (capsule or liquid via enteral route, including nasogastric/PEG/PEJ) following baseline observations being performed (i.e. temperature, heart rate, blood pressure, respiratory rate, skin check). The implicated penicillin will be administered if known. Amoxicillin will be administered for “penicillin unspecified” allergy labels (or penicillin VK if the reaction occurred prior to the availability of amoxicillin). The penicillin challenge dose will be charted by the study or ICU clinician (following review of baseline observations) and administered by bedside nursing staff. Clinical observations will be collected by the bedside nursing staff at + 30, + 60, + 90 and + 120 min post-oral challenge. If at any stage an antibiotic-associated adverse event is noted, the treating and study clinicians will be informed. Treatment of the adverse event will be at the discretion of the treating clinician.

Patients will undergo a repeat single-dose oral penicillin (250 mg) challenge (if initial challenge is negative) following ICU discharge and at least 48 h post-initial challenge (if they remain an inpatient). Participants who no longer require ICU-level care but have not yet been transferred out of the unit due to bed availability may receive the repeat oral challenge within the ICU if at least 48 h have passed since the primary challenge dose. A further set of clinical observations at 30-min intervals over 2 h will be collected following the repeat oral challenge. The repeat challenge is administered to assess for a potential false-negative initial oral challenge secondary to critical illness. Participants will be reviewed at 24 h and 5 days post-randomisation; 24 h and 5 days post the second oral challenge and 90 days post-randomisation. Participant review will assess for any serious or antibiotic-associated adverse events as per protocol definitions and will be undertaken in-person whilst an inpatient or via telephone or telehealth following hospital discharge. Participants with a positive initial challenge will not proceed to a repeat challenge.

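### The serious adverse event list has no item for prolongation of an existing stay, so a reaction whose only serious consequence is a longer index admission is not an SAE

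*Protocol article*

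**What the plan says.** The Harms section defines an SAE by six numbered outcomes. An adverse drug event qualifies if, in the investigators' opinion, it "is causal for any of these outcomes: (1) death; (2) life-threatening reaction; (3) inpatient hospitalisation". The fourth item is lasting or significant disability, and the list closes with "5) congenital anomaly or birth defect; or (6) requires intervention to prevent permanent impairment or damage". Item (3) is the only one that concerns hospital stay. No item covers a longer existing stay or other medically important events.

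Table 2 requires each participant to be an "Adult (≥ 18 years) ICU inpatient", and adds: "Are expected to stay in the ICU at least 24 h post-assessment". The Intervention section places the repeat challenge "following ICU discharge and at least 48 h post-initial challenge (if they remain an inpatient". It also allows that challenge inside the ICU for patients who are waiting only for a bed.

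Three things depend on the definition:
- **Primary safety outcome.** Table 1 counts patients who "experience an antibiotic-associated immune-mediated adverse event OR serious adverse event", judged against a limit of less than 5%.
- **Ethics reporting.** The Harms section states: "SAEs that occur from the time of commencement of study treatment to 5 days after the second challenge/observation will be collected". They are reported to the ethics committee within 24 h.
- **Adjudication.** The Data monitoring section states: "Any serious adverse events or antibiotic-associated immune-mediated adverse events will be referred to two independent clinicians". There is no data monitoring committee.

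**The concern.** A hospitalisation criterion detects harm by a change of state, from not being in hospital to being admitted. Here both challenges are given to people already in hospital, so that change cannot occur during the index admission. The corresponding harm for an inpatient is a delayed ICU or hospital discharge, and the list has no item for it.

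A reaction that delays discharge, but is not life-threatening or disabling and needs no intervention against permanent damage, would be left out of the SAE count and would not trigger the 24 h report. In some cases it would also be left out of the primary safety proportion. Any such omission can only make that proportion look more favourable. The length-of-stay outcome does not fill the gap: it is an exploratory comparison between groups and does not identify, report or adjudicate an individual harm.

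**Working it through.** **1. The plan's own figure.** The Sample size section projects 85 participants in a year: 200 eligible × 0.50 recruited × 0.85 completing = 85. This reproduces exactly, and the point does not depend on it. The same section gives the numbers used below: 80 enrolments, 40 per arm.

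**2. When can criterion (3) be met?**
- At the first challenge every participant is in the ICU (Table 2), so there can be no new admission.
- At the repeat challenge only those still in hospital are challenged (Intervention), so again there can be no new admission.
- After discharge but inside the SAE window, which ends 5 days after the second challenge or observation (Harms), a readmission would count.

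Criterion (3) therefore works for readmission only.

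**3. Which reactions are affected?** Take a reaction that lengthens the index stay and meets none of the other five criteria. The Harms section counts any immune-mediated reaction within 48 h of a dose, whatever its seriousness. It treats non-immune reactions as a separate category, and Table 1 does not include that category in the composite.

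| Reaction | Counted as an SAE, with 24 h report? | Counted in the primary safety outcome? |
|---|---|---|
| Immune-mediated, within 48 h of a dose | No | Yes, through the immune-mediated component |
| Immune-mediated, after 48 h | No | No |
| Non-immune, any time | No | No |

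The gap affects all three rows for SAE counts and reporting, and two of the three for the primary outcome. The protocol does look for late events, since reviews run to 5 days after each challenge or observation. After 48 h the SAE definition is the only way into the composite.

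**4. What is one missed patient worth?** Let n be the denominator and x the true number of patients with a qualifying event. Missing one patient reverses the verdict only if x/n ≥ 0.05 and (x − 1)/n < 0.05. Table 1 describes the denominator as patients with a penicillin allergy, which fits all 80 participants. The challenged arm alone would be 40. Both are shown, with exact (Clopper-Pearson) 95% intervals.

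| n | Patients with an event | Proportion | 95% CI | Below 5%? |
|---|---|---|---|---|
| 40 | 1 | 2.5% | 0.06 to 13.2% | Yes |
| 40 | 2 | 5.0% | 0.6 to 16.9% | No |
| 80 | 3 | 3.75% | 0.8 to 10.6% | Yes |
| 80 | 4 | 5.0% | 1.4 to 12.3% | No |

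Each missed patient lowers the proportion by 1/40 = 2.5 percentage points, or 1/80 = 1.25 points. The verdict changes on one missed patient only when x = 2 with n = 40, or x = 4 with n = 80. Away from the boundary it does not: 1/40 and 0/40 both pass, and 3/40 = 7.5% and 2/40 = 5.0% both fail.

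**The case against.** The strongest reply is that the primary outcome is largely protected. The reaction of most interest in an allergy challenge is an immune-mediated one soon after the dose, and that enters the composite without any test of seriousness. Criteria (2), (4) and (6) would still catch the most severe events, and criterion (3) still catches readmission. The one cited ICU cohort reports 54 direct challenges, all uncomplicated, so the missed events may be very few. All of this stands. It limits the size of the point but does not close the gap in SAE counts and reporting.

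A reader might go further in three ways that the document does not support.
- **That a longer stay is the most likely serious harm here, so the safety proportion must be materially too low.** The article gives no rate of prolonging reactions. Only the direction of any error is known.
- **That any missed event matters at a 5% limit.** Only a true count exactly on the boundary is reversed by one miss, and every cut-off in a small sample behaves this way.
- **That events which the unblinded investigators think unrelated never reach independent review.** The Harms section has two independent reviewers judge both immune-mediated and non-immune reactions within 48 h of a dose. The investigators' opinion controls the SAE label, not every route to review. For later events no independent check of that opinion is described. However, requiring a causal link is a defensible choice in ICU patients, whose illness itself produces many serious events.

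It may also be said that the full protocol could word the definition differently. The article nevertheless states the six items as the definition and signals no omission.

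**Conclusion.** The point holds as a specific gap in a rule that the article states in full. In a trial where both challenges are given to inpatients, criterion (3) cannot register a longer index stay. For SAE counts and 24 h reporting, this affects reactions of every type. For the primary safety outcome, it affects only non-immune reactions and immune-mediated reactions more than 48 h after a dose.

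The number of such events is unknown, so no bias can be quantified. The effect on the verdict is confined to the boundary counts of 2 in 40 or 4 in 80, and the missed patient must have no other qualifying event.

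The conclusion assumes that the six items are read as written and that the full protocol, which is not shown, uses the same list. It is a worthwhile correction to the wording, not evidence that the safety assessment is unsound.

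**What to change.** Change criterion (3) to inpatient hospitalisation or prolongation of existing hospitalisation (ICU or hospital stay) caused by the adverse drug event, in both the SAE definition and the case record form. Keeping the causal link prevents stays lengthened by the underlying illness from being counted.

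The cost is one phrase, some additional events for investigators to assess and for the two existing adjudicators to review, and a safety proportion that may be slightly less favourable. The sample size, allocation and challenge schedule are unaffected. Sending every serious event to adjudication whatever the investigator's opinion is a separate and debatable trade-off, and this correction does not require it.

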**Methods:**

Critically ill patients in the intensive care unit (ICU) with low-risk penicillin allergy phenotypes (PEN-FAST score < 3) will be randomised 1:1 to direct oral penicillin challenge (single dose 250 mg oral amoxicillin or implicated penicillin) or routine care, followed by a 2-h observation period. Patients will receive a second oral challenge/observation prior to hospital discharge (with subsequent observation for 2 h). An assessment for antibiotic-associated adverse events will also be undertaken at 24 h and 5 days post each challenge/observation and again at 90 days post-randomisation. The primary outcome measures are feasibility (proportion of eligible patients recruited and protocol compliance) and safety (proportion of patients who experience an antibiotic-associated immune-mediated adverse event or serious adverse event).

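### Non-serious immune-mediated reactions starting more than 48 h after an antibiotic dose are left out of the primary safety outcome although reviews run to 5 days, and the first reviews have two different time origins

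*Protocol article*

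**What the plan says.** Table 1 of the protocol article defines the primary safety outcome as a composite: "Proportion of patients with a penicillin allergy who experience an antibiotic-associated immune-mediated adverse event OR serious adverse event". An observed proportion below the threshold decides the matter: "5% will be used as the determinant of safety".

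The Harms section gives the two components different windows.

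- On the immune-mediated component it says: "An antibiotic-associated immune-mediated adverse event will include any immune-mediated reaction within 48 h of an antibiotic dose judged by two independent reviewers". The clock starts at a dose of any antibiotic, not only the challenge dose.
- Serious adverse events are drug events judged causal by the investigators. They are collected from the start of study treatment to 5 days after the second challenge or observation period, with no 48-h limit.

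The review schedule is worded in two ways. The abstract places reviews "at 24 h and 5 days post each challenge/observation and again at 90 days post-randomisation". The Intervention section says "Participants will be reviewed at 24 h and 5 days post-randomisation", then 24 h and 5 days after the second challenge, then 90 days after randomisation. The Control section also times its first reviews from randomisation.

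On the content of the reviews, the Intervention section states: "Participant review will assess for any serious or antibiotic-associated adverse events as per protocol definitions". The Control section repeats this. The Harms section, however, says: "An antibiotic-associated adverse event will be defined as any non-immune mediated reaction".

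**The concern.** The trial schedules a contact at 5 days and has two independent clinicians to adjudicate what is found. A non-serious reaction that begins on day 4 after a single challenge dose can be found and confirmed as immune-mediated and still not enter the primary safety proportion, because the time limit removes it. The same reaction does count if the patient received another antibiotic, or the repeat challenge, in the preceding 48 h. Whether it is an event then depends on something other than the reaction.

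At stake is whether the below-5% conclusion is informed by delayed non-serious reactions at all. Two wording problems sit beside this. The first reviews have two time origins, and the text on what the reviews look for uses a label that, by the protocol's own definition, excludes immune-mediated events.

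**Working it through.** **1. The plan's own figure.** From the Sample size section: 200 eligible × 0.50 recruited × 0.85 completing = 85, as stated; 80 enrolments are planned, 40 per arm. No significance level or power is given, so there is no power figure to reproduce. Table 1 does not say whether the safety denominator is one arm or both, so 40 and 80 are both used below.

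**2. Which reactions count.** Applying the Harms definitions to adjudicated reactions (onset times chosen for illustration):

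| Reaction after the challenge dose | Other antibiotic dose in the 48 h before onset | In the primary outcome? |
|---|---|---|
| Non-serious, onset 36 h | No | Yes |
| Non-serious, onset day 4 | No | No |
| Non-serious, onset day 4 | Yes | Yes |
| Drug-related serious, onset day 4 | Either | Yes, as a serious adverse event |

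Only the second row is lost. The repeat challenge can be given from 48 h after the first, so it can itself be the dose that brings a day-3 reaction into the count.

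**3. Length of the gap.** The 5-day review looks back over 5 × 24 = 120 h. The definition covers 48 h. The difference is 120 − 48 = 72 h, or 3 of the 5 days.

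**4. Time origin.** Let D be the delay in hours from randomisation to the challenge. Under the body text the first reviews fall 24 − D and 120 − D hours after the dose. With D = 24 (an assumption; the visible text gives no maximum) they fall at 0 h and 96 h, that is, 4 days. In controls the observations start at randomisation, so nothing shifts. The 5-day review would come before the 48-h window closes only if 120 − D < 48, that is, D > 72 h. For smaller delays the time origin shortens post-dose review but does not by itself cause an event inside the 48-h window to be missed.

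**5. Effect on the 5% rule.** Observed proportions with exact (Clopper-Pearson) 95% intervals:

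| Events / n | Proportion | 95% CI | Below 5%? |
|---|---|---|---|
| 1/40 | 2.5% | 0.1 to 13.2% | Yes |
| 2/40 | 5.0% | 0.6 to 16.9% | No |
| 3/80 | 3.75% | 0.8 to 10.6% | Yes |
| 4/80 | 5.0% | 1.4 to 12.3% | No |

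**6. Sensitivity.** The documents give no rate of late non-serious reactions, so the rates here are assumptions. Let X be binomial with n patients and rate (counted rate + late rate), taking the two as occurring in different patients. The rule is met when X ≤ 1 for n = 40, or X ≤ 3 for n = 80. With a counted rate of 2%, the probability of meeting the rule is:

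| Late rate added | n = 40 | n = 80 |
|---|---|---|
| 0 points | 0.81 | 0.92 |
| 1 point | 0.66 | 0.78 |
| 2 points | 0.52 | 0.60 |
| 3 points | 0.40 | 0.43 |

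The first row is what the 48-h definition would show whatever the late rate, if no other antibiotic dose brings late reactions into the count.

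**The case against.** The strongest reply is that a review later than 48 h is no error. The 5-day contact can pick up, in retrospect, a reaction that began between 24 and 48 h, and it matches the end of serious-event collection. No section says that the visit exists to find non-serious reactions starting on days 3 to 5. This stands as far as it goes: the schedule is not self-contradictory. It does not explain why a confirmed immune-mediated reaction seen at that visit should be left out.

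The immune-mediated definition is phrased as what the term will include, which could be read as non-exclusive. The next sentence in Harms uses the same 48-h phrase in an outright definition, which favours reading it as a limit. If it is not a limit, the component has no stated window and still needs correcting.

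On timing, the control observations at randomisation mirror those after the challenge. The authors may therefore have treated challenge and randomisation as nearly simultaneous. The participant timeline is in a figure that is not available here, so only the visible text can be said to lack a maximum delay.

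Several stronger readings are tempting and are not supported:

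- *That the whole primary safety event must arise within 48 h.* The serious-event component has no such limit, so days 3 to 5 can contribute.
- *That timing from randomisation makes reactions go uncounted.* The counting window runs from the dose; the time origin is a separate inconsistency.
- *That the definition biases the comparison between arms.* The window opens with any antibiotic dose. The Discussion anticipates a change in the type of antibiotic, not in whether one is given, and the Statistical methods section names no between-arm safety test.
- *That reviews are meant to ignore immune-mediated events.* The Data monitoring section sends these events for adjudication, so the fault is one of terms, not of intent.

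**Conclusion.** The point holds in a limited form. Non-serious immune-mediated reactions with onset more than 48 h after the last antibiotic dose are outside the primary safety outcome, although a scheduled review can find them and adjudicators are in place to judge them. Drug-related serious events are unaffected up to 5 days after the second challenge or observation period. The different time origins in the abstract and body, and the use of a term defined as non-immune in the review text, are separate inconsistencies of wording.

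The size is modest and uncertain. One uncounted reaction changes the verdict only if the counted events already stand at 1 of 40 or 3 of 80; with none counted, one more gives 1/40 = 2.5% and the rule is still met. A larger effect requires late-reaction rates that the documents do not supply. The conclusion assumes that the 48-h phrase is a limit and that the rule is applied to the observed proportion, as Table 1 states.

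**What to change.** 1. Keep the present criterion of 48 h after any antibiotic dose. Add to it any adjudicated immune-mediated reaction with onset up to the 5-day review after each challenge, or after the matched observation period in controls. This ends where serious-event collection ends. Replacing the present criterion with a challenge-only window would be worse, because it would drop reactions to later antibiotic doses that are now captured.
2. Report onset at or before 48 h and after 48 h separately, and show the safety proportion both ways against the 5% threshold.
3. Reconcile the abstract, Intervention and Control sections to one time origin for the first 24-h and 5-day reviews: the challenge, or the matched observation period in controls.
4. Name immune-mediated events explicitly in the text on what the reviews assess.

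The visits and the adjudicators already exist, so no new data collection is needed. The costs are rewording, adjudication of any additional late reactions, and a reported event rate that may be slightly higher.
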